### Participants

#### Sample size

This study will be designed to compare the effectiveness of the Tai Chi group against the control group. Sample size calculations will be based on the change in the Pittsburgh Sleep Quality Index (PSQI) and the Visual Analog Scale (VAS) scores. The study will detect a 5-point difference between groups on the PSQI scores (Irwin et al., 2008) and a 1.96-point difference in the VAS scores (Bower and Irwin, 2016). A total sample size of 96 participants will achieve 90% power with an alpha of 0.05. However, considering a 10% drop rate, we plan to recruit 106 patients.

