### Statistical analysis

The statisticians and researchers will establish a statistical plan. It will contain baseline characteristics, treatment effects, adverse events, and attendance evaluations. All analyses will be conducted using the intention-to-treat method. Two independent sample t-tests will be used for analysis. Repeated measures analysis of variance will be used to examine the effects of VAS between the Tai Chi group and the control group. We will use the Wilcoxon-Signed Rank Test to assess non-normally distributed data. Continuous data will be expressed as mean ± standard deviation. The chi-square test will be used for categorical data. We will set the statistical significance at a *P*-value of < 0.05. Missing data will be processed according to the last observation carry-forward rules. We will use IBM SPSS Statistics version 25 (SPSS, Inc., USA) for data analysis.

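### For PSQI and VAS the observed distribution decides between a mean-based analysis and a Wilcoxon test, and the Wilcoxon route gives no group difference in points to set against the planned 5 and 1.96

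*Protocol article*

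**What the plan says.** All the analysis rules are in the Statistical analysis section of the Protocol article:

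- Default comparison: "Two independent sample t-tests will be used for analysis".
- Pain intensity: "Repeated measures analysis of variance will be used to examine the effects of VAS between the Tai Chi group and the control group".
- Fallback: "We will use the Wilcoxon-Signed Rank Test to assess non-normally distributed data".
- Reporting: "Continuous data will be expressed as mean ± standard deviation", with no separate rule for non-normal data.

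The Sample size section plans on differences in points: "The study will detect a 5-point difference between groups on the PSQI scores" and "a 1.96-point difference in the VAS scores". It also says "Sample size calculations will be based on the change in the Pittsburgh Sleep Quality Index (PSQI) and the Visual Analog Scale (VAS) scores" and "A total sample size of 96 participants will achieve 90% power with an alpha of 0.05".

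The Abstract describes the primary outcomes as changes in sleep quality and pain intensity, while the Primary outcomes section refers to the PSQI scores themselves. PSQI runs from 0 to 21 and VAS from 0 to 10. The inclusion criteria set no minimum on either scale.

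**The concern.** The fallback rule applies to any outcome and does not exempt PSQI or VAS. The analysis that decides a primary outcome is therefore settled only after its distribution has been seen. Three things follow if the switch is made.

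1. The trial is sized to detect 5 PSQI points and 1.96 VAS points. The signed-rank test is a paired or one-sample procedure, so it yields no between-group difference to set against those targets.
2. VAS is rated weekly and at weeks 8, 16, 32 and 40. Repeated measures ANOVA was named to use that structure, and a Wilcoxon test cannot carry it. Different visits of one outcome could also be judged by different tests.
3. Results are still shown as mean ± SD, so the P-value would concern ranks while the printed figures concern means.

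This is a separate matter from the naming of a paired test. Replacing signed-rank with rank-sum would correct the test but leave the data-driven choice in place.

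There is also a plausible trigger. Both scales stop at 0, and an effective treatment moves one arm towards that floor.

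**Working it through.** **Step 1: the plan's own figure.** The total of 96 cannot be reproduced forward, because no SD is given. It can be solved backward, assuming a two-sided 0.05 test and 48 per arm:

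n per arm = 2 (1.960 + 1.282)² SD² / Δ² ≈ 21.0 SD² / Δ²

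- PSQI: SD = 5 × √(48 / 21.0) ≈ 7.56
- VAS: SD = 1.96 × √(48 / 21.0) ≈ 2.96

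Both correspond to a standardised difference of about 0.66.

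**Step 2: does the planned effect by itself create non-normality?** Two equal normal groups d SDs apart, when pooled, have excess kurtosis −2(d/2)⁴ / (1 + (d/2)²)². At d = 0.66 this is −2 × 0.0119 / 1.23 ≈ −0.02, which is negligible. In simulation a Shapiro-Wilk test on pooled continuous scores rejects in about 5% of trials for d from 0.66 to 1.5, its nominal rate. It rejects in 10% at d = 2.0 and 71% at d = 3.0. Checking each arm separately gives about 1 − 0.95² = 9.75% by chance alone.

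**Step 3: how often the switch would fire.** Inputs from the article: the planned differences, the scale limits, and 48 per arm (96 / 2). Assumptions: normal scores (clipped to the scale for follow-up values), the means and SDs shown, and a switch when Shapiro-Wilk gives P < 0.05 in either arm. The planned effect is present throughout.

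| Variable | Assumed setting | Switch rate |
|---|---|---|
| PSQI change, integer | SD 3 / 4 / 5 / 7.56 | 23 / 17 / 13 / 10% |
| VAS change, continuous | SD 1.5 to 2.96 | 9–10% |
| VAS change, whole numbers | SD 1.5 / 2 / 2.5 / 2.96 | 96 / 58 / 34 / 24% |
| PSQI follow-up | control mean 12–14, SD 3–4 | about 19–23% |
| PSQI follow-up | control mean 10, SD 3 / 4 / 5 | 35 / 70 / 94% |
| PSQI follow-up | control mean 8, SD 3–5 | 98–100% |
| PSQI follow-up | control mean 8–14, SD 7.56 | 99–100% |
| VAS follow-up, continuous | control mean 6, SD 1.5 / 2 / 2.5 / 2.96 | 8 / 7 / 21 / 60% |
| VAS follow-up, continuous | control mean 5, SD 1.5 / 2 / 2.5 / 2.96 | 9 / 22 / 60 / 87% |
| VAS follow-up, continuous | control mean 4, SD 1.5 / 2 / 2.5 | 41 / 85 / 98% |
| VAS follow-up, whole numbers | control mean 4–6, SD 2 | 59–100% |

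The high rates come from scores piling up at an end of the scale or from coarse rounding. A VAS control mean of 7 with SD 2.5 gives 63%, through the upper limit. The row with SD 7.56 is high because so wide a spread reaches the limits from any of those means.

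**Step 4: what the switch costs or protects.** On clipped follow-up scores with no true effect, the plain t-test rejects in roughly 4–6% of trials, so the switch is not needed to protect the 5% level. With normal change scores at the implied SDs, power for the t-test and the rank-sum test is 88.5% and 87.2% (PSQI), and 90.3% and 88.8% (VAS). At smaller true effects (1.5–2 PSQI points, 1–1.3 VAS points) the two tests fall on opposite sides of 0.05 in about 5–6% of trials.

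**Step 5: can a rank method give points?** A two-sample rank analysis can, through the Hodges-Lehmann shift. In simulation it gave 4.95 against a mean difference of 4.92 (PSQI, SD 7.56), and 1.96 against 1.95 (VAS, SD 2.96). The article names no such estimate, and the paired test it does name offers no between-group shift.

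**The case against.** A reader might infer that, if Tai Chi works as planned, both primary outcomes would usually leave the mean-based analyses. The document does not support that. It gives no SD, baseline mean, follow-up mean or normality criterion. The Abstract and the Sample size section speak of change, and on fine-grained change scores the rate is close to what chance produces. Nor does the switch always fire more often when treatment works. For PSQI with control means of 12–14 and SD 3–4 it fires in 13–25% of trials with no effect, much as with the planned effect. For whole-number VAS at mean 6, SD 2, it fires in about 62% without an effect and 59% with it. This objection stands, and the point makes no claim about how often the switch would occur in this trial.

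A reader might also infer that no rank test can estimate a difference in points. That is too broad, as Step 5 shows. It is true only of the test named. Readers could also subtract the arm means themselves, but the resulting figure would not be the quantity that was tested.

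The other objection is that a normality fallback is conventional, and that its details belong to the statistical plan the article says will be written. How normality is judged can indeed be left there, and its absence is not the finding. The switch itself, though, is stated in the article and covers the primary outcomes. A later plan would have to reverse the rule, not merely fill it in.

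**Conclusion.** The point holds in a limited form. The Statistical analysis section lets the observed distribution of PSQI and VAS choose between a t-test or repeated measures ANOVA and a Wilcoxon test. Under assumed inputs the switch rate is about 10–25% for fine-grained change scores. It reaches about 60% or more chiefly when follow-up scores sit near a scale limit or VAS is recorded in whole numbers. These rates rest on assumed means, SDs, distributional shape and a per-arm Shapiro-Wilk check, none of which is in the document.

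The consequence is mainly one of interpretation. After a switch there is no between-group estimate in points from the deciding test, no use of the repeated VAS data, and a P-value detached from the mean ± SD. Type I error and power hardly move. This is a worthwhile, inexpensive improvement and not a threat to the trial's validity.

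**What to change.** For PSQI and VAS:

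- Delete the normality-based switch.
- Name one mean-based between-group analysis for each as primary, to be used whatever the observed distribution.
- Report the between-group difference with its 95% confidence interval, read against 5 points (PSQI) and 1.96 points (VAS).
- Keep an independent-groups rank test (rank-sum, with a Hodges-Lehmann shift if wanted) as a sensitivity analysis only.

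The cost is one or two sentences in the analysis section or the statistical plan, with no new data and no change in sample size. The downside is slight: with extremely skewed data the mean-based test could lose a little power, and the rank-sum sensitivity analysis would show it.

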## Methods

### Study design

This study design conducts an open-label, randomized, controlled trial. The study protocol was approved by the Ethics Committee of the Hospital of Chengdu University of Traditional Chinese Medicine in Sichuan Province on 06/06/2022 (ethics approval number: 2022KL-038-02). This trial is registered with the Chinese Trial Registry under the number ChiCTR2200064977. This protocol adheres to the Consolidated Standard of Reporting Trials (CONSORT) and the Standard Protocol Items: Recommendations for Interventional Trials (SPIRIT). This study will be conducted at the Hospital of Chengdu University of Traditional Chinese Medicine, Qing Yang District University for the elderly, and Ci Tang Street Community. We will compare the effects of the Tai Chi group against the control group on insomnia in elderly people with CNLBP. Baseline assessments and follow-up assessments will be conducted at weeks 8, 16, 32, and 40 to measure primary outcomes such as sleep and pain intensity as well as secondary outcomes such as quality of pain, range of motion, physical performance, social support, quality of life, attendance rate, and adverse events. The detailed schedule of patient interventions and outcomes is described in Table 1.

**Table 1 T1:** Schedule of patients, intervention, outcomes.

**Item**	**Week 0**	**Week 1–8**	**Week 8**	**Week 9–16**	**Week 16**	**Week 32**	**Week 40**

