#### Control group

The participants in the control group will not receive any interventions for 8 weeks. After 8 weeks, participants will be instructed to do Tai Chi exercises for 8 weeks for 60 min (10 min warm-up, a 40 min Tai Chi training program, and a 10 min cooldown) three times a week. Tai Chi group coaches will also instruct participants.

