## Discussion

This study will compare the effectiveness of Tai Chi in improving insomnia symptoms in elderly people with CNLBP in the Tai Chi group with that in the control group. Previous research showed that Tai Chi provides various benefits for older adults with CLBP, including improvements in functional abilities (such as balance, leg strength, and flexibility), psycho-spiritual support, and social support (Lee et al., 2020). That study was conducted with 18 participants, who were randomized into the Tai Chi group. In our study, 122 participants will be recruited. Previous studies suggest that Tai Chi has protective effects on neuromuscular function in aging individuals with non-specific low back pain, but no follow-up was reported (Zou et al., 2019; Liu et al., 2020). Our study will fill this gap by conducting a 24-week follow-up to evaluate the effects of Tai Chi on insomnia in people with CNLBP. Previous studies mostly focused on the functional benefits of Tai Chi (Wen et al., 2022; Yan et al., 2022). However, this study will aim to test the effectiveness of Tai Chi in treating insomnia in patients with CNLBP.

This trial will have several strengths that increase its validity and reliability. First, the randomized controlled trial design of the study allows for a fair comparison of the effects of Tai Chi on insomnia in patients with CNLBP. Second, the study takes into account multiple factors that affect sleep quality, such as physical, psychological, and social factors. Additionally, the protocol adheres to CONSORT and SPIRIT guidelines.

However, this study will also face some limitations. First, the high expectations of the participants in the Tai Chi group may influence the results. Second, there is a risk of high dropout rates during the waiting period. Finally, the research process may be affected by COVID-19.

The results of this trial may help improve sleep quality and reduce pain in people with CNLBP. Furthermore, they could advocate for the promotion of Tai Chi training as a therapeutic option to treat insomnia in elderly individuals with CNLBP. Tai Chi may be considered a viable therapeutic option for CNLBP patients with insomnia.

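### The stated last-observation-carried-forward rule can bias the group comparison, chiefly for PSQI, in a direction set by when and in which arm participants leave

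*Protocol article*

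**What the plan says.** The Statistical analysis section of the protocol article gives one rule for incomplete data: "Missing data will be processed according to the last observation carry-forward rules". It sets no limit by outcome, visit or arm. The same section says: "All analyses will be conducted using the intention-to-treat method". People who leave therefore stay in the analysis with filled values.

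On the design, the Control group section says: "The participants in the control group will not receive any interventions for 8 weeks". It continues: "After 8 weeks, participants will be instructed to do Tai Chi exercises for 8 weeks for 60 min". On timing, the Study design section says: "Baseline assessments and follow-up assessments will be conducted at weeks 8, 16, 32, and 40". Table 1 places PSQI at weeks 0, 8, 16, 32 and 40 only. It places VAS at those visits and also within weeks 1–8 and 9–16, and the Pain intensity section describes weekly ratings.

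On dropout, the Sample size section gives one overall figure: "considering a 10% drop rate, we plan to recruit 106 patients". The Discussion adds, as a limitation: "Second, there is a risk of high dropout rates during the waiting period". The Data collection section says that participants will be contacted when data are missing.

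**The concern.** Carrying the last value forward assumes that a score stays frozen once a participant is lost. This design strains that assumption in two places.

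- **Before week 8.** The only earlier PSQI value is baseline, so anyone lost by then is entered with zero change. In the Tai Chi arm this removes any benefit plus natural improvement. In the control arm it removes natural improvement only. The two errors cancel only by chance.
- **After week 8.** A control who misses the week-16 visit carries a score taken before any Tai Chi into weeks 16, 32 and 40. A Tai Chi participant lost in the same window carries a score taken after the course. One rule thus fills in different treatment states in the two arms.

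Only the control arm has a waiting period, so the risk named in the Discussion makes unequal dropout before week 8 plausible. At stake are the size of the effect on a primary outcome at week 8 and the reading of the later follow-up. In addition, filled values are analysed as if they had been measured, which misstates the uncertainty.

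**Working it through.** **Inputs from the article:** 96 evaluable participants, 106 recruited, 10% dropout, 1:1 allocation (53 per arm), a 5-point PSQI difference, and the visit schedule. **Assumptions, because the article gives no figures:** dropout by arm and period, natural improvement, and the SD.

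**The plan's own figure.** 96 × 1.10 = 105.6, rounded up to 106; 96 / 0.90 = 106.7, rounded up to 107. The target of 106 is reproduced to within one patient.

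**Week 8, PSQI.** Let m be natural improvement, e the true effect, and dT and dC the dropout before week 8 in the Tai Chi and control arms, unrelated to outcome. Then

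estimate = (1 − dT)(m + e) − (1 − dC)m, so bias = dC·m − dT(m + e).

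With equal dropout d the bias is −d·e, whatever m is.

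| m | e (truth) | dT | dC | Calculation | Estimate |
|---|---|---|---|---|---|
| any | 5 | 10% | 10% | 0.90 × 5 | 4.5 |
| any | 5 | 20% | 20% | 0.80 × 5 | 4.0 |
| any | 0 | 10% | 10% | 0.90 × 0 | 0 |
| 2 | 3 | 5% | 25% | 4.75 − 1.50 | 3.25 |
| 2 | 3 | 30% | 10% | 3.50 − 1.80 | 1.70 |
| 2 | 0 | 5% | 25% | 1.90 − 1.50 | 0.40 |

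The effect is inflated only when dC·m exceeds dT(m + e). That requires some natural improvement and clearly heavier control dropout. Otherwise it is diluted or unchanged.

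**Weeks 16 to 40, PSQI.** Assume that training gives a 5-point gain in both arms, that the gain is kept, and that untreated scores do not change. The true difference is then 0 if every control would have trained.

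- Lost between weeks 8 and 16: Tai Chi participants carry the gain and controls carry none. False difference = dC × 5, that is 0.5 at 10%, 1.0 at 20% and 1.5 at 30%.
- Lost before week 8: both arms carry baseline. False difference = (dC − dT) × 5, that is 0 when dropout is equal and (0.30 − 0.05) × 5 = 1.25 at 5% against 30%.

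**Scale.** The article states no SD. Solving 48 per arm, 5 points, two-sided 0.05 and 90% power backwards gives 5 / (3.24 × √(2/48)) ≈ 7.56. The standard error with 53 per arm is 7.56 × √(2/53) ≈ 1.47, so 0.4 points is about 0.27 standard errors and 0.5 about 0.34. With an SD of 4 the standard error is 0.78, and the ratios are about 0.5 and 0.64.

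**Simulation of the week-16 case.** 53 per arm, 4,000 runs, t-test on PSQI change, random dropout after week 8, true difference 0 under the assumptions above. Rejection rate at nominal 5%:

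| Dropout (Tai Chi / control) | LOCF, SD 7.5 | LOCF, SD 4 |
|---|---|---|
| 10% / 10% | 5.8% | 9.3% |
| 20% / 20% | 10.3% | 23.3% |
| 5% / 30% | 16.7% | 43.5% |

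With observed values only, the same scenarios gave 4.4% to 5.4% and bias near 0.

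**VAS.** With weekly ratings, a participant lost before week 8 carries baseline only if lost before the first rating, and a control lost during weeks 9–16 may carry a partly treated score. The PSQI figures do not transfer to VAS.

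**The case against.** Several points on the other side have force.

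- **Size at the planned rate.** With 10% dropout in each arm the week-8 error is dilution, which is conservative, and it vanishes when there is no effect. Every rate above 10%, the natural improvement and the SDs are assumptions. This stands, and it limits the severity.
- **What the Discussion says.** A reader might infer that the article predicts heavy control dropout and so a bias towards Tai Chi. It names only a risk, gives no rate, and speaks of the waiting period, weeks 0 to 8. It says nothing about losses between weeks 8 and 16, so the post-crossover figures cannot rest on it.
- **What counts as false after crossover.** A control who never trained may really still be in an untreated state. For that person the carried score is wrong only against the value expected had they trained. This stands for never-trained controls. It does not help for a control who trained for most of the course and then missed the week-16 visit, whose untreated PSQI is still carried.
- **Later visits.** By week 16 both arms have had Tai Chi, so no missing-data method makes those visits a comparison with no treatment. That is a separate matter of design.
- **Mitigation and the unseen plan.** Contacting participants may reduce missingness, and sensitivity analyses may be in the announced statistical plan. Their absence here is not the point. The point is the rule that the article does state.

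**Conclusion.** The point holds in conditional form: the rule can bias the comparison, and timing and arm of loss decide the direction. For PSQI at week 8 the error is a loss of 0.5 points from a true 5 at equal 10% dropout. With unequal dropout it can go either way, for example a false 0.4 points at 5% against 25% with natural improvement of 2 and no effect. After crossover, controls lost between weeks 8 and 16 create a false 0.5 points at 10% loss and 1.0 at 20%, measured against the value expected had they trained and assuming that a 5-point gain is kept. The other outcomes scheduled only at visits share the mechanism.

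Two stronger readings are not supported. One is that the rule always biases the result, or always favours Tai Chi: equal early dropout cancels after crossover and dilutes the effect at week 8. The other is that both primary outcomes are equally affected: for VAS the carried value is usually a recent rating. That filled values are treated as measured follows from the rule itself; its effect on the standard errors was not calculated.

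This should be fixed before analysis. At the planned dropout the effect is modest, so it does not by itself invalidate the trial.

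**What to change.** In the Statistical analysis section, replace the carry-forward sentence with a likelihood-based mixed model for repeated measures on all observed values, with baseline, group, visit and group-by-visit terms. State that the effect of Tai Chi against the waiting list is read from the week-8 contrast. The same model can serve VAS, where the article now says: "Repeated measures analysis of variance will be used to examine the effects of VAS between the Tai Chi group and the control group".

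Add one multiple-imputation sensitivity analysis that departs from missing at random, for example by shifting the imputed values by arm.

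**Cost.** Wording and slightly more analysis work; no extra data, and the named software has a mixed-model procedure. The main analysis would rest on missing at random. After crossover it would implicitly credit lost controls with the gain of those who trained, which is one reason for the sensitivity analysis. Participants with only a baseline PSQI add nothing to the week-8 estimate if baseline is only a covariate. Modelling baseline as one of the repeated measures keeps them in the analysis set.

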## Discussion

This study will compare the effectiveness of Tai Chi in improving insomnia symptoms in elderly people with CNLBP in the Tai Chi group with that in the control group. Previous research showed that Tai Chi provides various benefits for older adults with CLBP, including improvements in functional abilities (such as balance, leg strength, and flexibility), psycho-spiritual support, and social support (Lee et al., 2020). That study was conducted with 18 participants, who were randomized into the Tai Chi group. In our study, 122 participants will be recruited. Previous studies suggest that Tai Chi has protective effects on neuromuscular function in aging individuals with non-specific low back pain, but no follow-up was reported (Zou et al., 2019; Liu et al., 2020). Our study will fill this gap by conducting a 24-week follow-up to evaluate the effects of Tai Chi on insomnia in people with CNLBP. Previous studies mostly focused on the functional benefits of Tai Chi (Wen et al., 2022; Yan et al., 2022). However, this study will aim to test the effectiveness of Tai Chi in treating insomnia in patients with CNLBP.

This trial will have several strengths that increase its validity and reliability. First, the randomized controlled trial design of the study allows for a fair comparison of the effects of Tai Chi on insomnia in patients with CNLBP. Second, the study takes into account multiple factors that affect sleep quality, such as physical, psychological, and social factors. Additionally, the protocol adheres to CONSORT and SPIRIT guidelines.

However, this study will also face some limitations. First, the high expectations of the participants in the Tai Chi group may influence the results. Second, there is a risk of high dropout rates during the waiting period. Finally, the research process may be affected by COVID-19.

The results of this trial may help improve sleep quality and reduce pain in people with CNLBP. Furthermore, they could advocate for the promotion of Tai Chi training as a therapeutic option to treat insomnia in elderly individuals with CNLBP. Tai Chi may be considered a viable therapeutic option for CNLBP patients with insomnia.

